# Self-administered acupressure for allergic rhinitis: study protocol for a randomized, single-blind, non-specific controlled, parallel trial

**DOI:** 10.1186/s13063-019-3495-0

**Published:** 2019-06-25

**Keywords:** Hay fever, Allergic disease, Acupuncture, Self-massage, Evidence-based Chinese medicine

## Abstract

**Background:**

Allergic rhinitis (AR) is an IgE-mediated inflammatory disease. Current conventional therapies for AR are unsatisfactory. Acupuncture has been recommended as an optional treatment for AR patients who are interested in non-pharmacotherapy in the new clinical practice guidelines for AR. Acupressure is a sub-type of acupuncture which is non-invasive with a low risk and can be self-administered. However, the current limited evidence is compromised by the high risk of bias and heterogeneity of methodology. Therefore, rigorously designed randomized controlled trials (RCTs) are needed. This proposed RCT aims to evaluate the efficacy and safety of self-administered acupressure for the management of AR.

**Methods/design:**

We have designed a randomized, single-blind, non-specific controlled, two-arm, parallel clinical trial involving a 2-week run-in period, a 4-week intervention period and an 8-week follow-up period. The eligible participants will be randomized into either a specific or a non-specific acupressure group. They will be required to perform self-administered acupressure on either five specific acupressure points or five non-specific acupressure points, 1 min for each point, twice a day for 4 weeks. Participants will be asked to complete self-administered questionnaires for outcome measures including a 7-point scale of symptom severity, the Rhinoconjunctivitis Quality of Life Questionnaire with Standardized Activities (RQLQs), relief medication scores, adverse events and participants’ opinion of this study at the different assessment points throughout the trial period. Data will be analyzed by the chi-square or *t* test using Statistical Package for Social Science (SPSS) software.

**Discussion:**

The findings from this study should provide scientific evidence for the efficacy and safety of self-administered acupressure for the management of AR. This study may assist the development of a non-cost, non-invasive self-management method for AR sufferers.

**Trial registration:**

Australian and New Zealand Clinical Trials Registry (ANZCTR), ID: ACTRN12617001106325 Registered on 28 July 2017.

**Electronic supplementary material:**

The online version of this article (10.1186/s13063-019-3495-0) contains supplementary material, which is available to authorized users.

## Background

Allergic rhinitis (AR) is an immunoglobulin E (IgE)-mediated immunologic inflammatory response of the nasal membrane after exposure to certain allergens which include pollens, dust mites, moulds, smoke, animal dander, air pollutants and occupational agents [1–3]. Patients with AR present with nasal symptoms such as sneezing, nasal itching, nasal congestion and a runny nose; which may be combined with non-nasal symptoms such as itchy and watery eyes, as well as an itchy and sore throat [2, 4]. AR has a high prevalence worldwide ranging from 10 to 30% of the population affected [5]. In Australia, AR is a common respiratory condition that affects approximately 20% of population and the cost of medication from the pharmacy suppliers increased from $107.8 million to $226.8 million between 2001 and 2010 [6, 7] . The troublesome nature of AR symptoms have a significant impact on patients’ quality of life such as work and school performance, sleep and mental health [2]. Moreover, AR has a high impact on asthma and is associated with rhinosinusitis and other comorbidities such as conjunctivitis and chronic cough [2, 6, 8].

Current management of AR includes allergen avoidance, pharmacotherapies (such as H_1_-antihistamines, corticosteroids, chromones, decongestants, anti-cholinergic drugs and anti-leukotrienes) and allergen-specific immunotherapy [2]. Most of the medications for AR are over-the-counter in Australia [6]. However, these medications are unable to provide full symptomatic relief and some of them are associated with undesirable side effects such as drowsiness and dryness in the nasal cavity. Systemic glucocorticosteroids cannot be used in the long term due to systemic side effects, such as suppressed immune system, osteoporosis, hypertension, diabetes, and especially impact on children’s growth [2, 3]. Those could be the major reasons for more and more patients with AR seeking help from complementary and alternative medicine including acupuncture [9].

Acupuncture has a long history for the management of AR. Currently, it has been recommended as an optional treatment for AR patients who are interested in non-pharmaceutical therapies in the Clinical Practice Guidelines for AR developed by the American Academy of Otolaryngology – Head and Neck Surgery and endorsed by the American Academy of Family Physicians [10]. Acupressure is a sub-type of acupuncture. It is a non-invasive therapeutic method applying physical pressure to certain acupuncture points by finger, elbow, hand or with various devices to treat diseases [11]. The popularity of acupressure has increased over recent years and has been the fourth preferred complementary and alternative therapy in hospitalized patients in Australia [12]. Several clinical studies have validated the effects of acupressure for various health conditions; for instance, nausea, vomiting and pain after caesarean delivery [13], hypertension [14] and constipation [15]. A systematic review of randomized controlled trials (RCTs) in acupressure for respiratory allergic diseases indicated that acupressure is safe for symptomatic relief of AR and asthma. However, no reliable evidence of efficacy could be identified due to the small number of included RCTs, the heterogeneity of the study design and a high/unclear risk of bias [16]. There is a need to perform rigorously designed RCTs to investigate the efficacy and safety of acupressure for the management of AR.

This study aims to investigate the efficacy and safety of self-administered acupressure on symptomatic relief and health-related quality of life improvement in adults with AR by conducting a superiority RCT. The study will also explore whether self-administered acupressure is effective in reducing the usage of Western medications in the management of AR.

## Materials/design

### Trial design

This study will be conducted at the Chinese Medicine Clinical Trial Laboratory in Royal Melbourne Institute of Technology (RMIT) University, Bundoora West and City campuses. It has been designed as a randomized, single-blind, non-specific controlled (i.e., using true acupuncture points without specific indications for AR in the control group), and two-arm parallel clinical trial according to the Guideline of National Statement on Ethical Conduct in Human Research 2007 (Updated May 2018) [17]. The trial will consist of a 2-week run-in period, a 4-week intervention period and an 8-week follow-up period. This study protocol was developed as required by the Standard Protocol Items: Recommendations for Interventional Trials (SPIRIT) (Additional file 1) [18] and the Revised STandards for Reporting Interventions in Clinical Trials of Acupuncture (STRICTA): extending the Consolidated Standards of Reporting Trials (CONSORT) Statement [19].

Ethics approval has been obtained from RMIT Human Research Ethics Committee (HREC) (project number: 20742). The RMIT HREC will oversee the conduct of this trial. The trial has been registered with the Australian and New Zealand Clinical Trials Registry (ACTRN12617001106325) (Additional file 2).

### Participants

The participants will be taken from the general population in Melbourne, Australia and recruited through advertisements on the Internet, posters, notice boards, leaflets, media release, social media, local newspapers, and newsletters. Participation in this research project is voluntary. The participants will be selected according to the inclusion and exclusion criteria listed in Table 1 below.

**Table 1 Tab1:** Inclusion and exclusion criteria of participants

Inclusion criteria	Exclusion criteria
• Aged ≥ 18 years • ≥ 2-year history of AR • (+) skin-prick test • Currently not involved in other clinical trials • Agree to make themselves available for the period of the study • Provide written consent for participation • Will not travel overseas or interstate for 14 weeks of the trial period • Have access to a computer and the Internet	• Current systemic corticosteroid therapy • Other current active respiratory disease (e.g., asthma) • Have used acupuncture/acupressure for respiratory or allergic diseases within the last month • Structural defects of the upper respiratory tract • Practitioner of Chinese medicine, an acupuncturist or a practitioner of Chinese medicine • Pregnancy • Travel overseas or interstate in the 14 weeks of the trial period • History of HIV, hepatitis B or C • Nasal polyposis • Unable to read and write English

*AR* allergic rhinitis

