#### Non-specific self-administered acupressure

Participants in the non-specific acupressure group will apply self-administered acupressure on another five non-specific acupressure points which are true acupuncture points on the body but not specifically indicated for AR treatment according to literature including *Extra Luozhen*, GV20 *Baihui*, GB4 *Hanyan*, SI18 *Quanliao* and GB12 *Wangu* [11, 25].

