This RCT has been rigorously designed as a randomized, single-blind, non-specific controlled clinical trial to minimize risks of bias. An independent statistician will generate randomization numbers using computer software and the randomization number will be assigned to participants using sealed opaque envelops. This procedure ensures adequate randomization and allocation concealment of participants. Due to the nature of acupressure, blinding of the acupuncturist is impossible for this trial. However, participants will be blinded during the entire randomization and intervention processes. Selection of acupressure points in treatment and control groups can be challenging as the size of fingers limits the chance of choosing the non-actual points 1 to 3 cm next to the real points which is the most popularly used sham control method in acupuncture/acupressure RCTs [30, 31]. This RCT adopts specific and non-specific points which are in the same area but 3 to 4 cm in between in the treatment and control groups which aims to maximizes the possibility of achieving successful blinding of participants [32]. In addition, all the interventions and the outcome measures will be administered by participants themselves, which avoids involving third-party assessors to reduce potential performance bias since blinding of assessors is considered more important than blinding practitioners since blinded assessments are less likely to bring biases to subjective outcomes [33]. When dealing with missing data, we will utilize the Worst-Case-Scenario method and intention-to-treat approach to manage the attrition bias. It is ideal to employ objective measures such as serum allergen-specific IgE to further investigate the mechanisms of action of acupressure for AR management. However, it is not feasible in this proposed RCT due to limited funding.

In summary, this protocol offers a standard regimen to guide the conduct of a RCT. By performing the rigorously designed RCT, this research project should make a significant contribution to the literature on self-administered acupressure. It may lead to the adoption of self-administered acupressure as a low-risk, non-invasive, non-pharmaceutical intervention for AR and could also assist the self-management of AR.

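### The training exclusion in Table 1 names Chinese medicine practitioners twice and, as written, leaves students and non-practising graduates eligible, although they could recognise their allocation and every efficacy outcome is self-rated.

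*Protocol article*

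**What the plan says.** The section Participants makes Table 1 the selection rule: "The participants will be selected according to the inclusion and exclusion criteria listed in Table 1 below". The table's only criterion on training excludes a "Practitioner of Chinese medicine, an acupuncturist or a practitioner of Chinese medicine". The nearest other criterion concerns treatment received, not training: "Have used acupuncture/acupressure for respiratory or allergic diseases within the last month".

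The control points are described as "true acupuncture points on the body but not specifically indicated for AR treatment according to literature". Under Interventions, each participant is trained individually and given a picture of the points to press. The Discussion states that "participants will be blinded during the entire randomization and intervention processes". It also says that participants administer the outcome measures themselves, without third-party assessors, and that objective measures were not feasible.

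On setting and recruitment, the trial is "conducted at the Chinese Medicine Clinical Trial Laboratory in Royal Melbourne Institute of Technology (RMIT) University", and "The participants will be taken from the general population in Melbourne, Australia and recruited through advertisements on the Internet, posters, notice boards, leaflets", followed by further media channels.

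**The concern.** A three-item list whose first and last items are identical is a drafting slip. Another group was probably meant, but the article does not say which. Read as it stands, the criterion does not reach people who have studied the points without practising.

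This matters because of the type of control. The two arms perform the same procedure on real points and differ in which points are pressed and what those points are indicated for. Someone who has studied point indications could tell from the picture which set they were given. Randomisation balances the number of such people across arms but not the direction of their ratings: belief in the points may improve scores in the specific arm, and disbelief may worsen them in the control arm. The t test cannot separate that difference from the point-specific effect that the trial is meant to estimate.

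**Working it through.** **1. What the criterion covers.** Item 1 is a Chinese medicine practitioner, item 2 an acupuncturist, and item 3 repeats item 1. Two distinct groups remain. No other entry in Table 1 mentions training. The one-month rule concerns use for respiratory or allergic disease, so a student who has never been treated passes it.

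**2. Whether recognition is possible.** The section on specific acupressure says that the active points were chosen from classical and modern literature. The section on non-specific acupressure says that the control points lack an indication for allergic rhinitis in the literature. Participants see the locations. A person taught that literature has what is needed to tell the sets apart.

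**3. The plan's own figure.** Section Sample size: effect size 0.6505, 80% power, significance level 0.05, 10% dropout, 45 per group. Data analysis: two-sided tests.
- Normal approximation: 2 × (1.960 + 0.842)² / 0.6505² = 37.1, so 38 per group; 38 / 0.9 = 42.2, so 43.
- Two-sample t test: 38.08, so 39 per group; 39 / 0.9 = 43.3, so 44.

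Both are within two participants of 45. The figure is not in dispute, and correcting the criterion does not change it. With 10% dropout, 45 × 0.9 = 40.5, so about 40 per arm complete.

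**4. Illustrative size (assumed inputs).** The article gives neither the share of trained volunteers nor the effect of recognition on ratings. Let a share k of each arm recognise its points, and let those people's ratings differ between arms by g SD beyond any true effect. Then:

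bias = k × g (in SD)

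With no true effect, the two-sided rejection probability comes from the noncentral t with 78 degrees of freedom and noncentrality bias / √(2/40).

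| k | g | bias (SD) | share of 0.6505 | type I error |
|---|---|---|---|---|
| 5% | 0.5 | 0.025 | 4% | 5.1% |
| 5% | 1.0 | 0.05 | 8% | 5.6% |
| 10% | 0.5 | 0.05 | 8% | 5.6% |
| 10% | 1.0 | 0.10 | 15% | 7.3% |
| 20% | 0.5 | 0.10 | 15% | 7.3% |
| 20% | 1.0 | 0.20 | 31% | 14.3% |

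In people, 5% is about 2 per arm (45 × 0.05 = 2.25) and 20% is 9 per arm, or 18 of 90. Nothing in the article supports the higher shares for a sample from the general population. The lower rows are the more cautious reading.

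**The case against.** The strongest reply is that only a wording slip is certain. The article condenses a fuller protocol, and the general and screening questionnaires mentioned under Recruitment are not shown; they may already ask about training. This stands in part. A reader might infer that students are being admitted in practice, and the article does not show that. It does show that Table 1 is the list used for selection and that, followed literally, it lets them in.

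A second reply is that recruitment is from the general population through many channels. That is correct. A reader might link the posters and notice boards with the campus laboratory and conclude that trained volunteers will be common. The article does not say that the notices are on campus or that students are targeted, so enrolment of such people is possible but of unknown frequency.

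A third reply is that there are safeguards. The Discussion describes specific and control points in the same area, 3 to 4 cm apart, and Secondary outcome measures includes a questionnaire on expectancy and credibility of blinding at the end of the first and final intervention weeks. It would therefore be too strong to say that blinding has no other support. But spacing does not mislead someone who knows the indications, and the questionnaire can detect loss of blinding without preventing it.

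Finally, one might extend the gap to people trained in point-based massage and to laboratory staff. The text does not carry that far. The Background treats acupressure as a form of acupuncture, so its practitioners are arguably covered already, and enrolment of staff is speculation. The supportable gap is students and non-practising graduates.

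**Conclusion.** The point holds as a defect in an eligibility rule. As written, the criterion repeats one group and leaves students and non-practising graduates of Chinese medicine or acupuncture eligible. In this design they could recognise their allocation while rating every efficacy outcome themselves.

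The size of any bias is unknown. At a few percent of participants it is small: about 0.03 to 0.05 SD and a type I error of 5.1% to 5.6% at k = 5%, conditional on the assumed gap of 0.5 to 1.0 SD and 40 completers per arm. The 14.3% in the table needs the highest share and the largest gap together, and should not be read as an expected error rate. That the missing item was meant to be students is likewise an inference; the omission itself is a fact. The correction is worth making because it is cheap and protects the comparison on which the trial rests.

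**What to change.** - **Table 1.** Replace the repeated item with: *current or former student or graduate of Chinese medicine or acupuncture*. If another group was intended, name it.
- **Screening.** Ask one question about such training in the existing screening questionnaire, if it does not already do so.
- **Participants already enrolled.** Trial status says that recruitment is in progress. Identify anyone with such training before randomisation, from the general questionnaire or one follow-up question, and repeat the primary comparison without them as a sensitivity analysis. Training before randomisation is a baseline characteristic, so the restricted comparison remains randomised.

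The cost is one line in Table 1, one question, a minor ethics amendment and one additional analysis. A few volunteers may be turned away. The planned sample size does not change. If few or no trained people are found, the sensitivity analysis will differ little from the primary one, which is itself worth reporting.

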### Sample size

The sample size was calculated using the program G*Power 3.1.9 [20]. Due to the absence of a similar acupressure study, the sample size estimation was based on an acupuncture study [21] that is closest to our study as we feel that using the acupuncture study would produce the best possible estimates of effect size and sample size. The effect size estimate in this acupuncture study was based on the main outcome variable (i.e., total nasal symptom score) which is also used in our study. We have also inflated the estimated sample size to cater for a 10% dropout which normally occurs in studies involving acupuncture. The effect size estimate is 0.6505. To achieve 80% power at the significance level 0.05 we need 45 subjects per group taking into consideration a 10% dropout rate.

### Recruitment

People who are interested in taking part in this trial will be provided with a Participant Information Sheet with Consent Form (PIS-CF) and asked to complete a general questionnaire and screening questionnaire if they agree with the PIS-CF. Written consent will be obtained from each participant by the investigators before an initial interview. The activities in the initial interview will include the allergen skin-prick test, a physical examination and a Chinese medicine differential diagnosis [22] to achieve an AR diagnosis. The participants meeting the inclusion criteria will enter the 2-week run-in period. During this period, every participant will be asked to conduct two sets of weekly baseline assessment including a 7-point scale symptom severity assessment form [23], a Rhinoconjunctivitis Quality of Life Questionnaire with Standardized Activities (RQLQs) [24] and a medication usage form. All baseline assessment forms will be submitted in the first intervention session. Figure 1 outlines the procedures of the clinical trial.

**Fig. 1 Fig1:**
[figure not shown]
Flow chart of the clinical trial procedures

### Randomization and blinding

To minimize bias, eligible participants will be randomized into either the specific acupressure treatment group or the non-specific acupressure control group with an allocation ratio of 1:1. Randomization will be conducted after baseline assessment using a computer program run by an independent researcher who is not directly involved in the trial. The randomization codes will be put into individually sealed opaque envelopes with sequel trial numbers. The sealed opaque envelopes contain the information on the location of specific or non-specific acupressure points for self-administered acupressure. Each participant will be asked to pick one sealed envelope from the pack of all the envelopes and pass it onto the registered acupuncturist. This acupuncturist is the only person who knows the participants’ group allocation in the trial. Neither the participants nor other investigators (such as data entry personnel and data analyst) will know the participants’ allocation to receive specific or non-specific acupressure treatment. The randomization codes and the allocation of the participants will be revealed once the RCT is completed. However, in the event of the need of this grouping information (e.g., a participant experiencing severe adverse events), the investigators will access the grouping data on the request of the physician. The relevant information will be documented in the participant’s case report form.

### Interventions

After randomization, the registered acupuncturist will provide detailed instructions and training on self-administered acupressure techniques to each participant individually. A pictorial instruction showing the location of acupressure points will be provided to the participants for further reference. Participants will be asked to perform self-administered acupressure on either five specific or non-specific acupressure points following the sequence from point 1 to point 5. The points will be self-pressed with maximal tolerable pressure but still within the comfortable range for 1 min each point, twice a day for 4weeks and complete the self-assessment on a weekly basis. During the treatment period, participants are required to have a weekly visit to the Clinical Trial Laboratory and the registered acupuncturist will monitor their skills to ensure the accurate performance of self-administered acupressure techniques. Messages will be sent to each participant to remind them to continue performing acupressure and attend the Clinical Trial Laboratory during each week. Figure 2 below illustrates the location of five specific acupressure points and five non-specific acupressure points.

